## Abstract

**Background:**

The extent of the benefits of exercise training during pregnancy on maternal, fetal, and neonatal health outcomes has not been sufficiently addressed. While aerobic exercise training has been determined as safe and efficacious throughout pregnancy, the effects of other training modes on fetal health and development as well as any continued benefits for the neonate, especially with regards to cardiovascular development and function, is largely unknown. In the ENHANCED by Mom study we aim to determine the effects of different modes of exercise training (aerobic, circuit, and resistance) throughout pregnancy on childhood health by controlling individual exercise programs and assessing the effects of each on fetal and neonatal health adaptations.

**Methods/Design:**

ENHANCED by mom is a cross sectional comparison study utilizing 3 intervention groups in comparison to a control group. Participants will complete three 5 min warmup + 45 min sessions weekly from 16 weeks to 36 weeks gestation of aerobic, resistance, or circuit training, in comparison to non-exercising controls. Maternal physical measurements will occur every 4 weeks throughout the intervention period. Fetal morphometric and heart measurements will occur at 34 weeks gestation. Neonatal measurements will be acquired at birth and at 1 month, 6 months, and 12 months.

**Discussion:**

A better understanding on the effects of exercise training during pregnancy on fetal and neonatal health could have a profound impact on the prevention and development of chronic diseases such as obesity, hypertension, and diabetes.

## Background

Understanding the effects of exercise during pregnancy on the fetus and neonate is just beginning to be explored. The effects of aerobic exercise on maternal health have been long understood, with the body of research indicating the safety and efficacy of maternal exercise training regarding fetal and neonatal health is growing [1–13]. The fetus is not at risk of hypoxia or significant bradycardia during maternal exercise [4, 9, 14–16]. The neonate of exercising women is also not at risk of being born disproportionately or underweight, but is similar to women who have not exercised. Moreover, fetuses of exercising women have decreased body fat mass compared to fetuses of non-exercising mothers [6].

Previous research has shown fetal adaptations in response to maternal aerobic exercise training, including heart rate modulation and improved autonomic control [10, 13, 17]. The fetal heart adapts similar to the adult heart when exposed to exercise training. For example, fetuses of exercising women had improved cardiovascular autonomic control indicated by decreased heart rates and increased HRV, relative to those of non-exercisers [10, 13]. Further analysis demonstrated a dose–response relationship, indicating that an increase in maternal exercise intensity and time spent participating in physical activity results in a greater fetal cardiovascular adaptation (i.e. decreased fetal HR and increased fetal HRV) [13]. A recent study reported that both continuous (aerobic) and intermittent (strength) exercise training throughout pregnancy are positively correlated to fetal cardiovascular adaptations [12]. May et al. [12] observed that intermittent exercise (i.e. strength exercises) throughout pregnancy may increase fetal heart adaptability compared to continuous exercise training (i.e. aerobic exercise) throughout pregnancy [12]. While fetal HRV can be altered with exercise, the effects of maternal exercise on fetal cardiac compliance remain elusive [10, 13, 18]. Cardiac compliance improves during normal maturation of the healthy neonatal heart [19, 20]. Exercise training in childhood further contributes to these natural increases [2]. However, since the cardiovascular and endocrine response differs with exercise type (i.e. aerobic, strength), the adaptation differs accordingly. For example, aerobic exercise in children is associated with lower heart rate, blood pressure, and lower lipid levels; conversely, resistance training in children has little or no change in heart rate, blood pressure, and lipid levels [21, 23]. However, both forms are known to decrease body fat composition [22]. It is currently unknown if the fetal physiological adaptation to exercise type is similar to the response of exercise in children as a result of in utero exposure to maternal exercise.

These studies have focused primarily on maternal aerobic exercise training or self-reported physical activity [9, 10, 12, 13, 17], measuring fetal HR and HRV. A scarce amount of research exists regarding the effects of other training modes, such as resistance training or circuit training during pregnancy, on fetal health and development as well as any continued benefits for the neonate, especially with regards to cardiovascular development and function. Research to date has only determined that various modes of maternal exercise training do not present undue risk to fetal or neonatal development [2, 24–26].

The primary aim is to determine the effects of different modes of exercise training (aerobic, circuit, and resistance) throughout pregnancy on health until the first year of life. The study presented will control individual exercise programs of varying modes throughout pregnancy to assess the effects of each on fetal and neonatal health adaptations.

We hypothesize that we will find: (1) lower measurements of maternal resting heart rate, weight gain, and body fat composition in women as follows: aerobic trained group = combination training group < strength training only group < < control group; (2) lower fetal HR, and increased infant HRV, stroke volume & cardiac output at 34 weeks gestation, 1, 6, and 12 months postnatal when exposed to various modes of maternal exercise compared to fetuses of women in the control group with greatest differences in aerobic trained group = combination training group > strength training only group > control group; and (3) normalized weights with lower fetal and birth body fat measures (i.e. BMI, body fat percentage) of all exercising groups compared to controls.

The purpose of this paper is to present the design and methodology of the Enhanced Neonatal Health and Neonatal Cardiovascular Efficiency Developmentally (ENHANCED) by Mom pregnancy study.

## Methods

### Study design

This study will be a cross sectional comparison using convenience sampling. All protocols have been approved by the East Carolina University Institutional Review Board. Informed written consent will be obtained from each participant prior to enrollment. The intervention period will begin at 16 weeks gestation and continue to 36 weeks gestation. Participants will be screened and enrolled between 13 and 16 weeks gestation to avoid any prevalent bouts of morning sickness and spontaneous abortion, which may occur and complete a pre-intervention appointment with a supervised submaximal exercise test. A visual description of the study’s methodology is presented in Fig. 1.

**Fig. 1 Fig1:**
[figure not shown]
Schematic Timeline of ENHANCED by Mom project

### Study population

This study aims to recruit women with low risk, singleton pregnancy who have received a physician’s clearance to participate in physical activity; those that were previously sedentary or active; between the ages of 18 and 40; a pre-pregnancy body mass index (BMI) 18.5-34.9; gestational age ≤16 weeks; not currently using alcohol, tobacco, recreational drugs, or medications for mental health disorders; and not currently meeting any of the contraindications to exercise in pregnancy as outlined by the American College of Sports Medicine (ACSM) and the Society of Obstetricians and Gynecologists of Canada guidelines (Table 1) [8, 27, 30]. Participants with pre-existing diabetes, hypertension, or other cardiovascular disease are excluded from the study. Participants with comorbidities known to affect fetal growth or well-being such as systemic lupus erythematosus are excluded from participation. Any participant diagnosed with gestational diabetes mellitus (GDM) during the study will remain enrolled in the study, but their results will be analyzed separately from other participants.

**Table 1 Tab1:** Contraindications to aerobic exercise during pregnancy. Adopted from *ACSM's guidelines for exercise testing and prescription [*
43]

Absolute Contraindications to Aerobic Exercise During Pregnancy	Relative Contraindications to Aerobic Exercise During Pregnancy
Hemodynamically significant heart disease	Severe anemia
Restrictive lung disease	Unevaluated maternal cardiac arrhythmia
Incompetent cervix/cerclage	Chronic bronchitis
Multiple gestation at risk for premature labor	Poorly controlled type I diabetes
Persistent second or third trimester bleeding	Extreme morbid obesity
Placenta previa after 26 weeks gestation	Extreme underweight (body mass index <12)
Premature labor during the current pregnancy	History of extremely sedentary lifestyle
Ruptured membranes	Intrauterine growth restriction in current pregnancy
Pregnancy induced hypertension	Poorly controlled hypertension/preeclampsia
	Orthopedic limitations
	Poorly controlled seizure disorder
	Poorly controlled thyroid disease
	Heavy smoker

### Study setting

Exercise testing will take place at an approved university exercise facility supervised by at least two certified (ACSM, First Aid, and CPR) staff members. In addition, exercise training sessions will be directly supervised (one-on-one) by a study staff member with an ACSM and/or personal trainer certification or who has been trained by a certified staff member on the study protocol. Exercise training will be modified within study parameters to participant preferences, choosing 3 days to attend supervised sessions at one of two approved university facilities between 7:00 a.m. and 7:00 p.m. Monday through Friday and 8:30 a.m. to 11 a.m. on Saturdays. Maternal measurements will be completed prior to exercise training at the appointed time. Local medical offices will be used for fetal ultrasounds, neonatal cardiovascular measurements, and neonatal body composition measurements.

### Recruitment

Participants will be recruited by brochures at local obstetrics clinics, as well as an email announcement to institutional faculty and staff. An inclusion and exclusion criteria card will be used by clinic staff to inform eligible patients of the study and determine individual interest in participation. These criteria will also be used by study staff to screen possible participants requesting more information regarding the study.

### Sample size

Power analysis was done based on our preliminary data and ANOVA to detect differences among the four groups post training. To ensure a power of 80 % and a significance level of 0.05 for each aim, 1) we will need a minimum of 15 participants per group (maternal HR) and a maximum of 70 per group (maternal body composition), 2) fetal and infant heart measures, we will need a minimum of 9 (fetal HR) and maximum of 21 per group (infant HRV), 3) we will need a minimum of 3 participants per group (birth weight) and a maximum of 22 per group (infant body composition). In order to detect differences minimum differences in all aims, we will need to recruit 3–70 participants per group. Therefore, we will aim for 70 per group plus an average participant attrition of 35 % inherent in long-term exercise intervention studies, we will recruit 380 participants (95 per group).

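### The 35% attrition allowance is applied as 70 × 1.35 instead of 70 / 0.65, so 95 per group leaves about 62 completers and about 74%, not 80%, power for maternal body composition

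*Protocol article*

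**What the plan says.** The Sample size section of the protocol article bases the calculation on "ANOVA to detect differences among the four groups post training" and sets the operating characteristics as follows: "To ensure a power of 80 % and a significance level of 0.05 for each aim". It then gives a smallest and largest requirement per group for each of three aims: 15 (maternal heart rate) to 70 (maternal body composition), 9 (fetal heart rate) to 21 (infant heart rate variability), and 3 (birth weight) to 22 (infant body composition). The largest of these sets the study size: "a maximum of 70 per group (maternal body composition").

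The allowance for losses follows: "we will aim for 70 per group plus an average participant attrition of" 35%, which the text describes as typical of long exercise trials. The result is that "we will recruit 380 participants (95 per group"). No effect size or standard deviation is given for any outcome, and no other section gives a different recruitment target or another route to 95.

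**The concern.** A sample size that comes from a power calculation is a number of women analysed. If 70 per group must remain and 35% of those recruited are expected to leave, the number to recruit is 70 divided by the retained fraction, 0.65. The protocol appears to have added 35% of 70 to 70 instead. That protects the target only against a smaller loss than the one it assumes.

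At stake is the power for maternal body composition. This outcome alone sets the study size, and body fat is named in the first hypothesis (Background). A reader who relies on 80% power when interpreting a null body-composition result would be relying on a figure that the protocol's own inputs do not deliver.

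**Working it through.** **Inputs, all from the Sample size section**

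- Test: one-way ANOVA, k = 4 groups, alpha = 0.05, power 80%
- Evaluable number required for the driving outcome: n = 70 per group
- Attrition: d = 0.35
- Recruitment target: 95 per group, 380 in total

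**Step 1. Reproduce the stated 95**

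- n × (1 + d) = 70 × 1.35 = 94.5, rounded up to 95; 4 × 95 = 380. This matches.
- n / (1 − d) = 70 / 0.65 = 107.7, rounded up to 108; 4 × 108 = 432. This does not match.

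So the stated figure comes from multiplying by 1.35.

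**Step 2. What 95 per group leaves**

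- 95 × 0.65 = 61.75 per group; 380 × 0.65 = 247 in total.
- Shortfall against the target: 70 − 61.75 = 8.25 per group.
- Largest attrition at which 95 still leaves 70: 1 − 70/95 = 26.3%.
- Check of the corrected figure: 108 × 0.65 = 70.2 per group.

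**Step 3. Power for maternal body composition**

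Because the protocol states no effect size, I solved for the Cohen's f that its own statement implies. Power is the probability that a noncentral F variable with 3 and 4n − 4 degrees of freedom and noncentrality 4n·f² exceeds the central F critical value at alpha 0.05.

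- Setting power to 80% at n = 70 gives f = 0.199 (noncentrality 280 × 0.1987² = 11.06).
- Holding f fixed and lowering n:

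| Completers per group | Power |
|---|---|
| 70 | 80.0% |
| 62 | 74.4% |
| 61.75 | 74.2% |
| 61 | 73.6% |

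- The effect detectable with 80% power at 61.75 per group is f = 0.212, against 0.199 at 70.

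**Step 4. Sensitivity to the choice of test**

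I also calibrated a two-group comparison of means to 80% power at 70 per group and evaluated it at 61 to 62 per group. Power is 74.4% to 75.1% unadjusted, 73.5% to 74.3% with Bonferroni for three comparisons, and 72.9% to 73.8% for six. The loss is about 5 to 7 points in every case.

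**Step 5. The other outcomes**

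The same back-calculation for requirements of 22, 21, 15, 9 and 3 per group gives power of about 99.9% or more at 61.75 per group. Only the outcome that needs 70 is affected.

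**The case against.** The arithmetic itself is not in dispute. The objections concern how much follows from it.

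- **One outcome only.** Five of the six stated requirements are untouched. The primary aim in the Background concerns health up to the first year of life, and the infant and fetal requirements lie far below 62. This stands, and the conclusion is limited to maternal body composition. It does not remove the error, because the section promises 80% power for every aim and that outcome sets the study size.
- **The 74% is conditional.** It rests on an effect size solved backwards and on the unadjusted post-training ANOVA named in the Sample size section. The Statistical analysis section also plans covariance adjustment for baseline. If f = 0.199 refers to the unadjusted analysis, a baseline–outcome correlation of about 0.35 would bring power back to 80% at 61.75 per group, and 0.50 would give about 87%. Those correlations are assumptions; the protocol gives none and does not use adjustment to justify 95. The caveat stands: 74% tests the protocol's claim against its own inputs and does not forecast the trial's actual power.
- **Further exclusions may or may not add to the loss.** The Statistical analysis section drops women below 80% compliance and analyses those with gestational diabetes separately. The protocol does not say whether the 35% already includes them. If they came on top, at purely assumed rates of 10–20% and 5–10%, about 44 to 53 per group would remain and power would be 58% to 67%. This is an illustration only, and the conclusion does not need it: even if the 35% covers every loss, 95 leaves about 62.
- **The practical shift is small.** The detectable effect moves from f = 0.199 to 0.212, and 95 is sufficient if attrition stays at or below 26.3%. Both statements are correct. They bear on how serious the error is, not on whether it is one.

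**Conclusion.** The concern holds. The target of 95 per group is reproduced by 70 × 1.35 and not by the correct 70 / 0.65. Under the stated 35% attrition it leaves about 62 women per group instead of 70. For maternal body composition the power is then about 74% instead of 80%, so the type II error rises from 20% to about 26%. The size of the loss assumes the effect implied by 80% power at 70 per group, equal groups, and an unadjusted four-group ANOVA at alpha 0.05. The error is plain and should be corrected, but its reach is modest: it affects one maternal outcome, and the fetal, infant and remaining maternal requirements stay well covered.

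**What to change.** Correct the attrition sentence in the Sample size section in one of two ways:

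1. Keep 380 and restate what it delivers: 95 per group with 35% attrition gives about 62 evaluable women per group, which is about 74% power for the maternal body composition effect originally assumed, or 80% power for f of about 0.21. Add that the other outcomes keep at least 80% power.
2. State that keeping 70 completers per group at 35% attrition would need 108 per group, 432 in total, which is 52 more than 380.

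The first is sufficient. In either case, add a sentence saying whether the 35% includes women excluded for low compliance and those analysed separately for gestational diabetes.

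The first option costs wording only, and a slightly less favourable stated power. It changes no endpoint, analysis or study procedure.

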### Intervention

Upon enrollment in the study, participants will complete an initial testing appointment. Upon arrival, a non-fasting venous sample will be collected, processed, and stored for later analysis of maternal factors (i.e. blood glucose). All participants will perform submaximal VO_2_peak treadmill testing using a modified Balke protocol as validated and replication by Mottola et al. [31] in order to determine individual THR zones. In order to enhance retention, we will utilize a restricted randomization process, in which the content of each protocol will be explained to participants and they provide us with two or three group preferences of which they are then randomized into one of those groups. Participants in the circuit training and resistance training groups will complete 1 repetition maximum testing on Cybex machines after completion of the treadmill exercise test to determine appropriate external loads for exercise training. This will also be used as a time for proper instruction on the technique of each exercise used. Upon completion of pre-exercise testing, participants will complete a modified physical activity questionnaire [32] to determine pre-pregnancy activity levels and a nutrition questionnaire [33] to ensure that participants are maintaining adequate diet and nutrition levels not only for increased energy needs of pregnancy, but also for the increased energy needs of exercise. These questionnaires will be completed a second time at the end of the intervention period to verify maternal activity and nutrition levels throughout the duration of the study [29].

#### Exercise protocols

All groups, including controls, will begin each exercise session with a 5-min aerobic warm-up of low intensity (i.e. treadmill speed ≤3.0 mph) followed by their respective protocols. HR will be monitored using a Polar FS2C heart rate monitor and maintained in the THR range determined by each participant’s pre-exercise test, but not to exceed THR ranges validated for pregnant women [34]. Moderate intensity will be maintained using the Borg scale of perceived exertion [35], with the goal of 12–14 for moderate intensity, as well as the “talk test,” which means being able to converse while exercising without feeling short of breath.

The aerobic training group will perform aerobic exercise using treadmills, ellipticals, or recumbent bicycles for a 45-min workout. Treadmill speed will be maintained at ≤3.0 mph, adjusting the percent grade to maintain the individual’s pre-determined THR range. Elliptical and recumbent bike resistance and speed levels will be adjusted as necessary throughout the study’s duration to maintain the individual’s pre-determined THR zone.

The resistance training group will perform 45 min of various resistance exercises. Two to three sets of 15 repetitions will be completed at a moderate resistance per ACSM guidelines for resistance training in pregnant individuals [29], using an RPE of 12–14 to maintain moderate intensity [36]. Resistance exercises will consist of seated Cybex machine exercises including leg extension, leg curl, shoulder press, chest press, triceps extension, and latissimus dorsi pull down. Dumbbells will be used for bicep curls, lateral shoulder raises, and front shoulder raises. Resistance bands and dumbbells will also be used as an alternative method for Cybex machine exercises if the participant is unable to maintain proper form or experiences discomfort in the machine’s positioning of the body. Core exercises will be completed on an exercise ball or bench for stability or side-lying on a mat, avoid supine positioning at all times, and vary among participants based on individual levels of comfort at the present stage of pregnancy. All exercises used will be selected from safe core exercises during pregnancy based on previous research findings [37]. Participants will progressively increase resistance of each exercise according to ACSM guidelines throughout the duration of the study [29].

The circuit training group will perform a circuit of aerobic and resistance exercises, devoting equal time to each, for a 45 min workout. After the warm-up, participants will rotate between 4.5 min of aerobic and resistance training exercises, for a total of 5 circuits. Resistance exercises will be 1 set of 15 repetitions, following that of the resistance training group, while aerobic training will be similar to the aerobic training group. An RPE of 12–14 will be used to maintain moderate intensity during resistance training exercises [36]. Throughout the study’s duration, each participant will progress accordingly with changes in the resistance and speed of aerobic training exercises as well as increases in resistance of the resistance training exercises. The continual switch between resistance and aerobic training exercises will be used to maintain the participant’s HR in the appropriate THR range throughout the exercise duration to induce a training effect similar to the aerobic training only group.

The control group will have personal coaching to perform daily activities only with a maximum participation of 45 min of stretching, breathing, and flexibility exercises. Stretches will target major muscle groups of the shoulders, triceps, legs, chest, and back. Breathing exercises will combine stretches with inhalation and exhalation techniques [38, 39]. Flexibility exercises will consist of transitions between stretches with controlled breathing techniques similar to low intensity yoga training. We will monitor their HR to be maintained at a low level, below each participant’s pre-determined THR range, not to exceed exertion levels above normal activities of daily living. A combination of seated, standing, and mat exercises will be included.

